## 15. Statistical Analysis

Statistical analyses will be performed using R (version 4.4.2; R Foundation for Statistical Computing, Vienna, Austria) or IBM SPSS Statistics (version 29.0; IBM Corp., Armonk, NY, USA). Continuous variables will be summarized as mean ± standard deviation or median with interquartile range, as appropriate, while categorical variables will be presented as counts and percentages.

The analytical framework is organized into four sequential tiers corresponding to the registry’s maturation. First, primary descriptive analyses will characterize patient demographics, comorbidity profiles, operative variables, and unadjusted outcome rates across the registry. These analyses will be performed from the outset of data accrual and will form the basis of annual national reports. Second, risk-adjusted benchmarking analyses will compare institutional outcomes after adjustment for case-mix using predefined clinical variables and established risk factors, with hierarchical models incorporating center-level random effects to account for clustering of patients within participating institutions. Third, validation analyses will evaluate the performance of existing international risk stratification systems, including EuroSCORE II and the STS risk models, within the Saudi cardiac surgical population. These analyses will be undertaken once a nationally representative dataset of sufficient size has been accrued. Fourth, risk prediction model development will be considered only after the minimum event threshold defined in the Risk Prediction Model section has been reached.

Within each tier, specific methods will be applied as follows. Comparisons between groups will be performed using Student’s *t*-test, Mann–Whitney U test, Kruskal–Wallis test, chi-square test, or Fisher’s exact test, as appropriate according to variable type and distribution. Time-to-event outcomes, including survival and freedom from MACCE, will be evaluated using Kaplan–Meier methods and compared using the log-rank test. Multivariable analyses will be conducted using regression models appropriate to the outcome of interest, including logistic regression for binary outcomes, linear regression for continuous outcomes, ordinal regression for ordered outcomes, and Cox proportional hazards models for time-to-event analyses. Propensity score methods, including matching and inverse probability of treatment weighting, will be reserved for specific pre-specified comparative sub-studies rather than applied as a general analytical approach.

Missing data will be evaluated routinely throughout the registry. Where appropriate, multiple imputation by chained equations will be used to address missing data, with complete-case analyses performed as sensitivity analyses to assess the robustness of findings. Patient-reported outcomes will be analyzed using validated scoring methodologies for the EQ-5D and SF-36 instruments. Longitudinal changes in patient-reported outcomes will be evaluated using linear mixed-effects models or generalized estimating equations where sufficient follow-up data are available, with minimally important clinical difference thresholds applied to contextualize observed changes.

Interim descriptive analyses may be performed during early registry implementation to evaluate feasibility, data completeness, follow-up performance, and outcome capture. All statistical tests will be two-sided, and a *p*-value of less than 0.05 will be considered statistically significant.

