### 12.1. Primary Objective

To determine the association between preoperative risk factors, intraoperative variables, and postoperative clinical outcomes following CABG surgery, including mortality, major adverse cardiac and cerebrovascular events (MACCE), deep sternal wound infection, and unplanned reoperation.

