## 19. Limitations

As participation is voluntary, variation in institutional engagement, data completeness, follow-up capture rates, and cardiac rehabilitation reporting may occur across participating centers. Participating institutions may also differ systematically from non-participating centers in case volume, resources, or outcomes, potentially limiting the generalizability of registry findings. Differences in local infrastructure, staffing, and data management capabilities may further contribute to variability in data quality across sites. Although standardized definitions, training programs, automated validation, and audit mechanisms are incorporated into the registry design, the accuracy and completeness of submitted data will ultimately depend on local data collection practices. Variation in local consent requirements may additionally affect case capture rates and registry representativeness.

As an observational registry, SCAR will be subject to the inherent limitations of registry-based research, including residual confounding, missing data, and variation in clinical practice patterns between institutions. Longitudinal follow-up may be affected by loss to follow-up and differential follow-up rates between centers, which could introduce bias into long-term outcome analyses. Development of robust benchmarking systems and locally relevant risk stratification tools will require accrual of sufficiently large datasets with adequate outcome events and sustained multicenter participation. Long-term sustainability will depend on continued institutional commitment, effective governance, robust technical infrastructure, and secure funding support and may be supported through phased implementation, pilot-phase evaluation, and continuous stakeholder engagement.

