Intraoperative	Operative Data	Date/time of surgery, surgical urgency (elective, urgent, emergency class 1–4), revascularization technique (on-pump, off-pump, HB-CPB, conversions), CPB use, CPB time, aortic cross-clamp time, graft type (arterial, venous, composite), number of grafts performed, number of distal anastomoses, cardioplegia type and temperature, epiaortic ultrasound, ascending aorta status, porcelain aorta, off-pump surgeon experience, concomitant Maze procedure, intraoperative blood product transfusion, intraoperative complications
Postoperative (In-Hospital)	In-Hospital Outcomes	ICU length of stay, prolonged ICU stay, hospital length of stay, discharge destination (home, rehabilitation facility, long-term care facility, other), duration of mechanical ventilation, re-intubation, myocardial infarction (Type V definition) [18], stroke (permanent/temporary, imaging-confirmed), deep sternal wound infection (CDC criteria) [19], leg wound infection, mediastinitis, reoperation (bleeding, tamponade, graft failure), early repeat revascularization (PCI/CABG), new-onset atrial fibrillation, ventricular arrhythmia, pericardial effusion requiring drainage, AKI (KDIGO), new renal replacement therapy, delirium requiring medication, VTE (deep vein thrombosis/pulmonary embolism), nadir Hb/Hct, blood loss in first 12 h, blood products transfused, prolonged inotropes (>12 h), postoperative IABP, ECMO, in-hospital mortality
30 Days	Follow-up Outcomes	All-cause mortality, wound complications, readmission (all-cause), MACCE, medication adherence, NYHA class, cardiac rehabilitation referral, cardiac rehabilitation participation
3 Months	Follow-up Outcomes	Recovery status, persistent symptoms (angina, dyspnea), medication adherence, wound healing, NYHA class, cardiac rehabilitation participation, return-to-work status (where applicable), EQ-5D, SF-36
6 Months	Follow-up Outcomes	Functional recovery (NYHA class), return to routine activity, interim MACCE, physical activity level, medication adherence, cardiac rehabilitation completion status, return-to-work status (where applicable), EQ-5D, SF-36

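### Centre effects are stated only for the benchmarking tier; the primary-objective association analyses sit in no tier, and the models and tests available to them carry no centre term

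*Protocol article*

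**What the plan says.** Section 12.1 sets the primary objective: "To determine the association between preoperative risk factors, intraoperative variables, and postoperative clinical outcomes following CABG surgery". Section 12 adds, as the registry's premise, that factors related to the institution as well as to the patient and the procedure are to be identified. Section 12.2 lists predictors of morbidity and mortality as one secondary objective and institutional variability with benchmarking as another.

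Section 15 has four tiers. In the first, "primary descriptive analyses will characterize patient demographics, comorbidity profiles, operative variables, and unadjusted outcome rates across the registry". The second is benchmarking between institutions, "with hierarchical models incorporating center-level random effects to account for clustering of patients within participating institutions". The third validates existing international scores. The fourth is prediction model development, deferred until the event threshold in section 13 is met. No tier names the association analysis of section 12.1.

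The section then introduces its methods with "Within each tier, specific methods will be applied as follows". It lists two-group and multi-group tests, the log-rank test, and multivariable regression, "including logistic regression for binary outcomes, linear regression for continuous outcomes, ordinal regression for ordered outcomes, and Cox proportional hazards models for time-to-event analyses". All tests are two-sided at 0.05. The only other correlated-data methods named are mixed models or generalized estimating equations for longitudinal patient-reported outcomes.

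The operative data in Table 1 include "revascularization technique (on-pump, off-pump, HB-CPB, conversions", together with graft type, cardioplegia and epiaortic ultrasound. Section 19 expects "variation in clinical practice patterns between institutions".

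**The concern.** Patients treated at one centre share surgeons, protocols and case-mix, so their outcomes are correlated. Two things follow when an exposure also varies by centre and the model has no centre term.

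- **Precision.** The model counts patients as independent information about a contrast that is partly a contrast between a few centres. The standard error is too small.
- **Confounding.** A centre with better or worse outcomes for other reasons passes that difference on to whatever technique it favours.

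The plan acknowledges clustering for one use of the data and does not carry that over to the objective it calls primary. Section 17 says that findings may inform guideline development and policy discussions, so a centre difference read as a technique effect would have consequences.

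**Working it through.** **What the text covers.** Benchmarking has centre random effects. The association analyses have no tier and no stated centre handling. The listed tests assume independent patients in their standard form.

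**No figure to reproduce.** The plan states no sample size, intraclass correlation (ICC), national centre count or standard error for these analyses. Everything below is a check under assumed inputs:

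- m = 300 patients per centre and 20 centres (assumed).
- Event rates of 6% (assumed, for a composite such as MACCE) and 2% (assumed; section 1 cites operative mortality of roughly 1.9 to 2.5% from the US database).
- Latent ICC of the outcome of 0.01, 0.02 and 0.05 (assumed).
- Share of exposure variation lying between centres, ICC_x, from 0 to 1 (assumed).

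**Formulas.**

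- Random-intercept variance: s² = ICC/(1 − ICC) × π²/3.
- Approximate ICC on the observed 0/1 scale: ICC_y = s² × p(1 − p).
- Design effect: DEFF = 1 + (m − 1) × ICC_y × ICC_x. The true standard error is √DEFF times the one reported by a model without centre.
- Actual two-sided error of a nominal 5% test: 2 × [1 − Φ(1.96/√DEFF)].

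**One case in full (6% events, latent ICC 0.02, exposure fixed by centre).** s² = 0.02/0.98 × 3.290 = 0.0671. ICC_y = 0.0671 × 0.06 × 0.94 = 0.00379. DEFF = 1 + 299 × 0.00379 = 2.13. The standard error ratio is 1.46 and the actual error is 0.18.

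**Simulation.** Random centre intercepts, a covariate with no effect, 1,000 replicates per cell, 20 centres of 300. The table shows the rejection rate of a logistic test without centre. The formula value is in brackets, with ICC_x = 1 for the centre-level factor, 0.5 for the partly centre-driven factor and 0 for the patient-level factor.

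| Events | Latent ICC | Centre-level factor | Partly centre-driven | Patient-level |
|---|---|---|---|---|
| 6% | 0.01 | 0.125 (0.117) | 0.079 (0.083) | 0.053 (0.050) |
| 6% | 0.02 | 0.201 (0.180) | 0.110 (0.117) | 0.064 (0.050) |
| 6% | 0.05 | 0.359 (0.322) | 0.206 (0.211) | 0.048 (0.050) |
| 2% | 0.01 | 0.072 (0.073) | 0.071 (0.061) | 0.049 (0.050) |
| 2% | 0.02 | 0.106 (0.097) | 0.084 (0.073) | 0.040 (0.050) |
| 2% | 0.05 | 0.181 (0.167) | 0.122 (0.110) | 0.039 (0.050) |

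The Monte Carlo standard error is √(0.05 × 0.95/1000) = 0.007 near 5% and √(0.359 × 0.641/1000) = 0.015 at the top.

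**Sensitivity.** With 10 centres of 200 and 6% events, the centre-level rates are 0.100, 0.155 and 0.263, and the partly centre-driven rates 0.074, 0.091 and 0.158. With 2% events they are 0.059, 0.092 and 0.133, and 0.051, 0.048 and 0.084. With no outcome clustering, all rates are about 0.04 to 0.06. A separate simulation of 400 runs per cell (20 centres of 300, 6% events) with exposure correlation 0.3 gave 9.0% at ICC 0.02 and 13.8% at ICC 0.05.

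**After correction.** A centre-aware test (stratified by centre, or at centre level for a centre-level factor) brings the error back to about 0.04 to 0.07 in every scenario.

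**The case against.** The strongest reply is that the text never says that clustering will be ignored. The list of models is open, and its lead-in applies it within every tier, including the one whose models are hierarchical. It can therefore be read as fixing the outcome family rather than the variance structure. This is a condensed article, and whether a regression carries a random intercept is often left to an analysis plan. The hierarchical benchmarking models also adjust for risk factors and so would yield associations. Table 1 records surgeon-level and patient-level determinants of technique, such as off-pump experience and porcelain aorta, so no named variable is shown to be set by the centre. Section 19 already concedes residual confounding.

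Much of this stands. A reader might infer that the primary-objective models are fixed as single-level and that their p-values are therefore wrong. The document does not support that, and the consequence is conditional. How far each practice variable is centre-determined is an assumption, and the top of the range applies only to a factor fixed entirely by centre.

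The reply does not remove the point. Where the authors want correlated-data methods they name them, for benchmarking and for repeated patient-reported outcomes. The primary objective gets neither a tier nor such a statement. Listing residual confounding as a limitation does not correct a standard error.

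**Conclusion.** The point holds in a conditional form: section 15 states centre effects for benchmarking only, and what it lists for the primary objective carries no centre term. Followed as listed, the methods overstate precision for exposures that vary by centre and can mix centre differences into their effects.

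Under the assumed 20 centres of 300 and latent ICC of 0.01 to 0.05, a nominal 5% test has an actual error of about 12 to 36% (centre-level factor) or 8 to 21% (partly centre-driven) at 6% events, and about 7 to 18% or 7 to 12% at 2% events. Fewer or smaller centres, rarer events or a lower ICC reduce this. For patient-level factors without between-centre differences, which may describe many preoperative variables, the error stays near nominal (0.039 to 0.064). It would be wrong to conclude that the whole primary objective is affected. The point is a clarification worth making before recruitment, not an error that invalidates the plan.

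**What to change.** In section 15:

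1. Assign the primary-objective and predictor analyses to a tier.
2. State that their multivariable models account for centre: a random intercept in logistic, linear and ordinal models, and a centre-stratified baseline hazard or shared frailty in Cox models. Cluster-robust variance with a few-centre correction is an alternative.
3. For practice variables, separate within-centre from between-centre effects, for example by adding the centre mean of the exposure or by using fixed centre effects. A random intercept alone does not remove confounding by centre, and robust variance does not address it.

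The pilot's feasibility summaries and the tier 4 prediction model need not be covered. P-values need not be dropped from unadjusted comparisons.

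The cost is a few sentences and standard software, and the article says that recruitment has not begun. The downside is wider intervals for centre-driven variables. Factors constant within a centre cannot be estimated under fixed centre effects.

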## 5. Pilot Phase

Registry implementation will commence through an initial pilot phase involving four selected tertiary cardiac surgery centers. The pilot phase is expected to enroll approximately 100–150 consecutive CABG procedures over a period of three months and is intended to evaluate operational feasibility, data completeness, follow-up capture rates, data quality processes, user experience, and platform performance before broader national implementation.

Key pilot success indicators will include a data completeness rate of at least 90% across mandatory fields, a 30-day follow-up capture rate of at least 80%, adherence to standardized variable definitions, usability of the electronic platform, and overall operational feasibility. Predefined thresholds for these indicators must be met before progression to national rollout is initiated. National expansion is anticipated to begin within 12 to 18 months of pilot phase completion, with the registry aiming to capture a substantial and progressively increasing proportion of CABG procedures performed at tertiary cardiac surgery centers across Saudi Arabia. Findings from the pilot phase will be used to refine registry procedures and inform the timeline and scope of subsequent national expansion.

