## 11. Data Collection and Follow-Up

Data for SCAR will be collected at standardized intervals beginning at hospital admission and continuing through one year postoperatively. The dataset is organized into domains aligned with international cardiac surgery registry standards while incorporating variables relevant to the Saudi healthcare context. Standardized definitions will be used across participating centers to ensure data consistency, facilitate benchmarking, and enable meaningful national and international comparisons. The complete list of domains, time points, and key variables is presented in Table 1.

Follow-up assessments will be performed at 30 days, 3 months, 6 months, and one year after surgery. Outcome ascertainment will be achieved through a hierarchical approach: outpatient clinic visits and hospital electronic medical records will serve as the primary sources of follow-up data, supplemented by review of readmission records and institutional follow-up databases where available. Direct telephone contact will be used when clinic-based or record-based ascertainment is not achievable. A minimum of three documented contact attempts will be made before a patient is recorded as lost to follow-up. Where available, linkage with national mortality records or Ministry of Health administrative databases may be explored to support outcome ascertainment, particularly for mortality endpoints. Participating centers will be encouraged to maintain accurate patient contact information and verify contact details at each follow-up encounter to minimize loss to follow-up.

Patient-reported outcomes will be assessed using validated Arabic and English versions of the EQ-5D and SF-36 instruments. Baseline assessments will be obtained preoperatively and repeated at 3 months, 6 months, and one year postoperatively to facilitate longitudinal evaluation of functional recovery and health-related quality of life. Administration may be performed in a clinic, by telephone, or electronically according to center capability and patient preference, with efforts made to minimize missing responses through standardized administration protocols. Follow-up data will include survival, major adverse cardiac and cerebrovascular events (MACCE), functional recovery, cardiac rehabilitation referral and participation, return-to-work status, and patient-reported outcome measures.

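### Complete-case analysis, the only named check on missing data, cannot show whether post-discharge outcomes are robust to loss that depends on the unseen outcome

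*Protocol article*

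**What the plan says.** Section 15 (Statistical Analysis) names its main method, to be applied where suitable: "multiple imputation by chained equations will be used to address missing data". The same sentence then describes the one accompanying check: "with complete-case analyses performed as sensitivity analyses to assess the robustness of findings". No other sensitivity analysis for missing data is named in the article. Weighting methods appear only for treatment comparisons in sub-studies. Survival and freedom from MACCE are to be analysed by Kaplan–Meier, log-rank and Cox methods, and centres are compared through models with random centre effects.

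Four other places bear on the point:

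- Section 19 (Limitations): "Longitudinal follow-up may be affected by loss to follow-up and differential follow-up rates between centers". The consequence is put as a possibility: "which could introduce bias into long-term outcome analyses".
- Section 5 (Pilot Phase) sets as a success indicator "a 30-day follow-up capture rate of at least 80" per cent. No capture target is given for one year.
- Section 11 (Data Collection and Follow-Up): "A minimum of three documented contact attempts will be made before a patient is recorded as lost to follow-up". For deaths in particular, "linkage with national mortality records or Ministry of Health administrative databases may be explored to support outcome ascertainment", which is not a commitment.
- Table 1 lists myocardial infarction, stroke and death among the in-hospital data, so events during the index stay are recorded before any patient can be lost.

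**The concern.** The article chooses one sensitivity analysis and gives its purpose, which is to judge robustness. For an outcome lost after discharge, that analysis leaves the critical assumption untouched.

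Imputation as normally run fills in a missing outcome as if lost patients had the same risk as followed patients with the same recorded data. A covariate-adjusted complete-case analysis of that outcome makes the same assumption, and a crude complete-case proportion makes a stronger one. If lost patients have more events than comparable followed patients, or fewer, both methods err in the same direction. Kaplan–Meier and Cox analyses likewise require censoring to be non-informative, and rerunning them on complete cases does not relax that.

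The direction cannot be settled from the document. Patients who died or were readmitted elsewhere may be harder to trace. Equally, events in a centre's own records may be easier to find than their absence. If capture also differs between centres, the error differs between centres and enters the benchmarking, while the planned check may report stability.

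**Working it through.** The plan gives no figure to reproduce here. The check asks what the two planned analyses would show if loss were related to the outcome.

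**Inputs.** From the protocol: 80% capture at 30 days (section 5), so up to 20% lost. Assumed: a 5% event rate among followed patients, the risk or odds multipliers for lost patients, 95% capture at a comparison centre, and the split of events before and after discharge.

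**1. Overall rate, multiplier applied to the whole rate.** True rate = c·q + (1 − c)·k·q, where c is capture, q the rate in followed patients and k the risk ratio in lost patients.

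- k = 2: 0.8 × 5% + 0.2 × 10% = 6.0%
- k = 3: 0.8 × 5% + 0.2 × 15% = 7.0%
- No lost patient has an event: 0.8 × 5% = 4%. Every lost patient does: 4% + 20% = 24%.
- The same bounds are 4.5% to 14.5% at 90% capture and 4.75% to 9.75% at 95%.

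**2. 30-day MACCE, multiplier applied only after discharge.** Assume 3 percentage points occur in hospital and are known for everyone, and 2 occur later among those followed.

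- k = 2: 3% + 0.8 × 2% + 0.2 × 4% = 5.4%
- k = 3: 3% + 0.8 × 2% + 0.2 × 6% = 5.8%

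Step 1 is therefore an upper illustration for 30-day MACCE.

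**3. Two centres that both observe 5%, with 5% and 20% lost and k = 2.**

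- Multiplier on the whole rate: 0.95 × 5% + 0.05 × 10% = 5.25%, against 6.0%.
- Multiplier after discharge only: 3% + 0.95 × 2% + 0.05 × 4% = 5.1%, against 5.4%.

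**4. Would the planned comparison reveal this?** A simulation used 200,000 patients in two centres with the same underlying risk, capture of about 95% and 80%, and one baseline covariate. Centre and covariate were both in the imputation model. The odds ratio (OR) links the event to loss, given centre and covariate. Rates are shown as centre A / centre B.

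| OR | True rates | Complete-case | Imputation | Adjusted centre OR: true | complete-case | imputation |
|---|---|---|---|---|---|---|
| 1 | 8.71% / 8.82% | 8.67% / 8.49% | 8.74% / 8.85% | 1.014 | 1.011 | 1.015 |
| 3 | 8.74% / 8.57% | 7.80% / 5.93% | 7.93% / 6.30% | 0.983 | 0.776 | 0.776 |
| 5 | 8.72% / 8.70% | 7.18% / 4.68% | 7.36% / 5.04% | 1.006 | 0.663 | 0.663 |

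At OR 1, loss depends only on centre and the recorded covariate, and imputation recovers the truth. At OR 3 and OR 5 the adjusted centre comparison is the same under both methods and wrong under both: the centre that loses more patients looks better. The exact agreement is expected, because imputation and analysis used the same variables. Further predictors in the imputation model could separate the two methods somewhat, but would not test whatever dependence on the outcome remains.

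**The case against.** Several objections deserve weight.

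- **Detail of this kind belongs in an analysis plan.** This is a condensed article, and silence on tipping points alone would not be a finding. But the article does not merely stay silent: it names a check and says what it is for. The point concerns that stated choice.
- **Complete-case analysis has real uses.** Regression coefficients from complete cases stay valid when missingness depends on covariates, even on their unseen values, but not on the outcome given covariates. Standard imputation can be biased there. In a registry with more than 100 variables that is a useful contrast. This stands, and is why complete-case analysis should be kept.
- **Much of 30-day MACCE is already known at discharge.** This stands and reduces the size, as step 2 shows.
- **The 80% figure is a pilot progression indicator, not a standing tolerance.** This also stands. Capture is monitored and fed back to centres, and contact attempts are layered. These measures reduce loss but do not test its mechanism.
- **An odds multiplier does not suit censored data.** Correct. The time-to-event analyses need their own version.

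A reader might infer that the protocol expects informative loss, or that loss differing by centre is itself the defect. The document supports neither. Section 19 says only that such loss may occur and could bias results, and it does not describe the loss as informative. The OR 1 run shows that loss explained by centre and recorded covariates is handled by imputation that includes them.

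**Conclusion.** The point holds for post-discharge outcomes: the later part of 30-day MACCE, one-year MACCE and survival, and centre comparisons of these. For them, agreement between complete-case analysis and standard imputation is not evidence of robustness to the follow-up bias that section 19 acknowledges as possible. In-hospital mortality and unplanned reoperation during the index stay are unaffected.

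The size is not determined by the document. For 30-day MACCE at 80% capture and an assumed 5% observed rate, 6% to 7% is an upper illustration, and 5.4% to 5.8% applies if three-fifths of events are known in-hospital events. One-year outcomes have the longer period at risk of loss, but no one-year capture figure is given, so no size is claimed for them. The multipliers are assumptions, and the bias could run the other way.

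It would go too far to say that the planned results are biased, or that complete-case analysis is always the stronger assumption and should be dropped. What is shown is that the named check does not vary the assumption that matters for these outcomes.

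**What to change.** Keep complete-case analysis as a comparison and add the following to section 15:

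- **Binary outcomes.** A delta-adjusted (pattern-mixture) multiple imputation for post-discharge 30-day MACCE and for one-year MACCE and mortality. Multiply the odds of an event in lost patients by a stated range, for example 1, 1.5, 2 and 3, overall and by centre. Report the tipping point, that is, the multiplier at which the conclusion changes. A value below 1 could be added, since the direction is uncertain. Events already recorded in hospital stay as observed.
- **Kaplan–Meier and Cox analyses.** Apply the same idea as a multiplier on the hazard after censoring.
- **Imputation model.** Include centre, so that it matches the hierarchical analysis and deals with loss explained by centre.

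The cost is a few sentences of text and a small amount of extra analysis. No new data are needed, and section 4 states that recruitment has not begun, so the change can be made before any outcome is seen.
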